### Sample size

As all the patients in this study will be selected on the basis of already having one or more potentially inappropriate prescriptions, the sample size calculations are based on a 100% prevalence rate. Separate sample size calculations were performed for the two primary outcomes:

#### Proportion of participant patients with PIP

The calculation is based on demonstrating a clinically relevant 10% absolute reduction (from 100% to 90%) in the proportion of PIP with 80% power and a statistical significance of 5% (one-sided), between the randomized groups. With a cluster design, the assumption that individual outcomes are independent of each other does not hold, as participants in the same cluster may respond in the same way. The sample size, therefore, needs to be adjusted to reflect this by use of the intraclass correlation coefficient (ICC) [43]. We used an ICC of 0.025, based on an ongoing unpublished observational study of an elderly cohort in the HRB Centre for Primary Care Research. With a maximum of ten patients per cluster and factoring in a loss to follow-up of 10%, a total of 22 GP practices and 212 patients will be required.

#### Mean number of PIP per patient

An ongoing unpublished observational study of an elderly cohort in the HRB Centre for Primary Care Research estimates a mean number of 1.45 inappropriate prescriptions per patient. To demonstrate a 30% relative reduction in the mean number of PIP (equivalent to a mean of 1.02), with 80% power and a statistical significance of 5% (two-sided), between the randomized groups, with a maximum of ten patients per cluster and factoring in a loss to follow-up of 10%, a total of 14 GP practices and 132 patients will be required.

These calculations indicate that we would need at least 22 practices and 212 patients to detect a difference between the intervention and control arms for both of our primary outcome measures. On the basis of these calculations, we aim to recruit at least 22 practices, with 10 patients per practice, giving a total of 220 patients. With this sample size, we would have at least 80% power to demonstrate a 10% absolute reduction in the proportion of PIP and a 30% relative reduction in the mean number of PIPs. Based on existing evidence that suggests that simple, less intensive feedback does not alter prescribing behaviour [35,36] we have not anticipated an improvement in the control arm. However, we will monitor for this in the parallel process evaluation.

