**Methods/design:**

This study is a pragmatic cluster randomized controlled trial, conducted in primary care (OPTI-SCRIPT trial), involving 22 practices (clusters) and 220 patients. Practices will be allocated to intervention or control arms using minimization, with intervention participants receiving a complex multifaceted intervention incorporating academic detailing, medicines review with web-based pharmaceutical treatment algorithms that provide recommended alternative treatment options, and tailored patient information leaflets. Control practices will deliver usual care and receive simple patient-level feedback on potentially inappropriate prescribing. Routinely collected national prescribing data will also be analyzed for nonparticipating practices, acting as a contemporary national control. The primary outcomes are the proportion of participant patients with potentially inappropriate prescribing and the mean number of potentially inappropriate prescriptions per patient. In addition, economic and qualitative evaluations will be conducted.

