Prednisolone (or equivalent) > 3 months or longer without bisphosphonate	Increased risk of fracture	N/A
NSAID with ACE-inhibitor	Risk of kidney failure, particularly with the presence of general arteriosclerosis, dehydration or concurrent use of diuretics	N/A
NSAID with diuretic	May reduce the effect of diuretics and worsen existing heart failure	N/A

ACEI, angiotensin-converting-enzyme inhibitor; COPD, chronic obstructive pulmonary disease; GI, gastro-intestinal; GORD, gastro-oesophageal reflux disease; N/A, not available; NSAID, nonsteroidal anti-inflammatory drug; PPI, proton pump inhibitor; p.r.n., *pro re nata*, as needed; SSRI, selective serotonin reuptake inhibitor; TCA, tricyclic anti-depressant. *Prevalence: the proportion of the study population with one or more potentially inappropriate medications.

The primary outcomes to be determined are the proportion of participant patients with PIP (as a composite measure, that is, any number of PIP criteria as listed in Table 2, to address the issue of multiple PIP in individual patients) and the mean number of potentially inappropriate prescriptions per patient.

Secondary outcomes (summarized in Table 3) will include individual measures of the composite measure, that is, drug-specific outcomes, process evaluations, process-of-care measures and patient-reported outcomes (Health status (EQ-5D) [38], Patients’ Beliefs about Medicine Questionnaire (BMQ) [39], Well-being Questionnaire (WBQ-12) [40]).

**Table 3 T3:** Secondary outcome measures

**Secondary outcome**	**Measure**
Drug-specific outcomes	The absolute number of PIPs per patient of the top five occurring PIP drugs: [11]
	Proton pump inhibitor (PPI) for peptic ulcer disease at full therapeutic dosage for >8 weeks
	Long-term (>3 months) use of NSAIDs for relief of mild joint pain in osteoarthritis
	Long-term (>1 month) use of long-acting benzodiazepines, for example, chlordiazepoxide, flurazepam, nitrazepam, chlorazepate and benzodiazepines with long-acting metabolites for example, diazepam
	Any regular duplicate drug class prescription
	TCAs with an opiate or calcium channel blocker
	Mean number of PIPs per patient of the top five PIP drugs (as above)
Patient-reported outcomes	Health status (EQ-5D)
	Patients’ Beliefs about Medicine Questionnaire (BMQ)
	Well-being Questionnaire (WBQ-12)
Process-of-care measures	Number of GP visits (6 months prior to enrolment and at 4 and 12 month follow-up)

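### Two primary outcomes each carry a full significance level, with no rule for which result decides effectiveness; if either suffices, the chance of a false claim of benefit is about 5.5% to 7.4%

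*Protocol article*

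**What the plan says.** The abstract and the Outcome measures section give both outcomes equal standing: "The primary outcomes are the proportion of participant patients with potentially inappropriate prescribing and the mean number of potentially inappropriate prescriptions per patient". Under Sample size, "Separate sample size calculations were performed for the two primary outcomes". The proportion is sized for a "clinically relevant 10% absolute reduction (from 100% to 90%) in the proportion of PIP", with "80% power and a statistical significance of 5% (one-sided"), which gives 22 practices and 212 patients. The mean number of PIPs is sized for a fall from 1.45 to 1.02, with "80% power and a statistical significance of 5% (two-sided"), which gives 14 practices and 132 patients.

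The larger figure is then taken as what is needed "to detect a difference between the intervention and control arms for both of our primary outcome measures". With 220 patients the article claims power of 80% or more for the two effects.

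The Plan of analysis names a family of multilevel models and the intention-to-treat principle. Its subgroup sentence refers to the primary outcome in the singular without saying which one. The Study aim and objectives section asks one question, whether the intervention is effective in reducing PIP.

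**The concern.** Two results feed one verdict, and the article does not say how. Each outcome has the significance level it would have if it were the only primary outcome. That is valid if both must succeed, or if they are tested in a fixed order. It is not valid at 5% if either one is enough.

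The two outcomes can disagree. Every patient enters with at least one PIP, and the expected mean of 1.45 implies that some have several. A patient who moves from two PIPs to one lowers the mean but still counts as having PIP. A trial could therefore be significant on the mean and not on the proportion. Without a prior rule, whether that is a positive trial would be decided after the results are known.

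**Working it through.** **Reproducing the stated sample size (proportion).** Inputs from the Sample size section: 100% versus 90%, one-sided 5%, 80% power, ICC 0.025, 10 patients per practice, 10% loss.

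- Uncorrected size per arm: n₀ = [1.645·√(2·0.95·0.05) + 0.842·√(1·0 + 0.9·0.1)]² / 0.1² = 57.7, or 58.
- Continuity correction: (n₀/4)·[1 + √(1 + 4/(n₀·0.1))]² = 76.4, or 77.
- Design effect: 1 + 9 × 0.025 = 1.225. 77 × 1.225 = 94.3, or 95.
- Loss: 95 / 0.9 = 105.6, or 106 per arm. The total is 212 patients in 22 practices, an exact match.
- Without the continuity correction the same chain gives 160, so the corrected formula appears to be the one used.

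**Mean number of PIPs.** The difference is 1.45 − 1.02 = 0.43. No SD is given, so the stated 132 cannot be checked independently. An SD of 0.75 reproduces it: 2·(1.960 + 0.842)²·0.75²/0.43² = 47.8, or 48; × 1.225 = 58.8, or 59; / 0.9 = 65.6, or 66 per arm; total 132 in 14 practices. Solving backwards from 132 without rounding gives 0.756, which is used below.

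**Either outcome suffices.** Under no effect, take the two test statistics as bivariate normal with correlation ρ. A false claim of benefit is Z₁ > 1.645 or Z₂ > 1.960, because the two-sided test of the mean puts only 2.5% in the direction of benefit. Any false rejection is Z₁ > 1.645 or |Z₂| > 1.960.

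| ρ | False claim of benefit | Any false rejection |
|---|---|---|
| 0 | 1 − 0.95 × 0.975 = 7.4% | 1 − 0.95 × 0.95 = 9.75% |
| 0.5 | 6.8% | 9.3% |
| 0.9 | 5.5% | 8.0% |
| Upper bound | 5% + 2.5% = 7.5% | 5% + 5% = 10% |

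The outcomes are linked by construction, since having any PIP means a count of at least one. Zero correlation is therefore an extreme case.

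**Both outcomes required.** The effective size per arm at 220 patients is 220 × 0.9 / 2 / 1.225 = 80.8.

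- Power for the proportion, one-sided 5%, continuity-corrected: 82.5%.
- Power for the mean, two-sided 5%, SD 0.756: 95.1%.
- Joint power: at worst 82.5 + 95.1 − 100, about 77.7% before rounding; 78.5% at ρ = 0; 80.3% at ρ = 0.5; 82.4% at ρ = 0.9.

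The result depends on the assumed SD. Power for the mean falls to 86% at SD 0.9 and 78% at SD 1.0, and joint power falls with it. In the other direction, without the continuity correction the proportion has about 90% power and joint power stays above 80%.

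**Could an alpha split be added later?** At one-sided 2.5% the proportion needs 93 per arm, then 114, then 127, for a total of 254 in 26 practices. Its power at 220 is about 73%. The mean at two-sided 2.5% keeps about 92%.

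**The case against.** The strongest reply is that a full level on each outcome is correct for two outcomes that must both succeed, and also for a fixed sequence. The stated levels therefore contradict nothing. Only the decision rule is absent, and a statistical analysis plan that is not shown may contain it. Much of this stands: the article nowhere says that either outcome suffices, and a later plan could supply a valid rule. What remains is that the sample size is already committed to unadjusted levels. An equal split could not be adopted later without taking the proportion to about 73% power at 220, and Trial status reports that 22 practices had already been recruited. The choice of rule is tied to figures the article has fixed.

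Two stronger readings are tempting and are not supported.

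- A reader might infer that effectiveness could be falsely claimed about 10% of the time. That figure counts a significant increase in PIP on the two-sided test of the mean as well. In the direction of benefit the bound is 7.5%.
- A reader might infer that the power claim is wrong. The calculations were done separately, and per outcome the claim holds at 220 (82.5%, and about 95% under the assumed SD). Even read jointly, the worst-case shortfall is about two points, and it rests on an SD the article does not state and on the continuity correction.

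**Conclusion.** The point holds, at moderate size. The article fixes two primary outcomes at full levels and seeks one conclusion, with no rule linking them. If either result is taken as success, the chance of a false claim of benefit is about 5.5% to 7.4% for correlations from 0.9 down to 0, against an intended 5%. If both are required, there is no inflation and joint power is close to the stated 80%. The error rates rest only on the stated levels and a bivariate normal approximation. The joint power figures also rest on the back-solved SD, an ICC of 0.025 for both outcomes, 10% loss and the continuity-corrected formula. The either-or ambiguity is the part that matters; the power question is minor.

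**What to change.** Before analysis, state one success rule that keeps the stated significance levels and sample size. One option is a fixed sequence: test the proportion of patients with PIP first, since it sets the sample size, and test the mean number only if the first test is significant. Say that effectiveness is concluded from the first test. Requiring both outcomes would also be valid, with joint power of about 78% to 82% under the assumptions above. Reword the closing power sentence to say that the figure is for each outcome separately.

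This costs a sentence or two and no patients. The downside of the sequence is that the mean number of PIPs cannot be claimed as confirmatory if the proportion is not significant.

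The sidedness of the proportion test should be treated as a separate matter and not changed as part of this fix. A two-sided 5% test of the proportion would have only about 73% power at 220, and would need 254 patients in 26 practices under the formula that reproduces 212.

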### Data management and protection

A trial steering committee will be established. The aim of the trial is to identify older patients with existing PIP. These patients will be known to the research team by study ID number only. One member of the research team (BC) will have access to patient contact details for follow-up data collection purposes. The GP remains responsible for all treatment decisions made. Informed consent will be sought from all study participants. All data collected will be stored on a secure, password-protected server. All interviews will be audio recorded and transcribed, the digital recording overwritten and the transcripts pseudo-anonymized and stored on a secure, password-protected server.

The academic detailing will demonstrate the process of the medicines review with the intervention practices but the research team will not monitor how the GP implements the study protocol after this, other than to remind the practices to complete the process within the allotted period. This study is pragmatic in nature, measuring the intervention’s effectiveness in real clinical practice.

### Ethical approval

Ethical approval was granted by the Research Ethics Committee of the Irish College of General Practitioners (ICGP). At the request of the Ethics Committee, some changes were made to the study protocol. The patient information letter and questionnaire were rewritten to be clearer and simpler for an older audience. Initially, it was proposed that a member of the research team (BC) would become a research agent of the practice, in order to minimize the effort required by the practice staff to recruit patients [44]. However, the ethics committee requested that the practices should be responsible for the patient consent process. The committee also requested that any prescribing pattern of concern identified by the research team should be referred to an external academic GP with no involvement in the trial to assess the case and to determine the necessary next steps; this arrangement has been put in place.

### Qualitative evaluation

A qualitative process evaluation will be conducted to explore participant attitudes towards the intervention and the experience of the intervention delivery. Specifically, semistructured interviews will be conducted with a sample of participants, both GPs and patients, from the intervention arm. The interviews will be structured using a topic guide, which will be developed with the stages of the interview in mind (introducing the research, beginning the interview, and so on) [45]. These interviews will address such research questions as:

1. What are the views of the participants about the acceptability, effectiveness and sustainability of the intervention?

2. What barriers, if any, were experienced by GPs in relation to implementing the alternative recommended treatments?

3. How did patients respond or react to the idea of altering their medication regimes?

4. Was the medicines review viewed as a useful exercise for the patient or the GP, or both?

5. In what ways might the intervention be modified or adapted to maximize its effectiveness in routine care?

A random sample of participants in the intervention arm will be invited to participate. The number of interviews required to reach data saturation (where no new themes emerge) will be considered, alongside feasibility issues (resources and timing), but a sample of 10 to 15 patients and 10 GPs is proposed [46]. For individual patients, the interviews will take place within one month of the medicines review. For GPs, the interviews will be conducted within one month of them completing their assigned reviews, that is, after all ten reviews for single-handed practices and after completion of assigned reviews in group practices. The interviews will be conducted either in person (in a setting of the participant’s preference) or via telephone. Telephone interviewing is generally used in qualitative research where time or cost is an issue and there is evidence that there is little difference in the answers obtained this way [47]. In this case, scheduling face-to-face interview time with GPs and older patients may be difficult, so telephone interviewing is an option. In addition, as part of the process evaluation, we will conduct brief telephone interviews with the control-group GPs to ascertain any potential impact of the feedback they receive based on the baseline data. Control-group participants will not be required to document any of the decisions made with regard to the control data, so this approach may be more prone to recall bias. However, we consider it a suitable option, given the limited time available in busy GP practices. All interviews will be audio recorded (on loudspeaker for telephone interviews) and transcribed. The data will be collated and a thematic analysis will be conducted. There are four main steps to conducting a thematic analysis:

1. Collect the data.

2. Identify patterns and themes (repetition).

3. Collate related patterns into subthemes.

4. Interpret themes in light of a literature review [48].

NVivo 9 will be used to assist with organizing the data for analysis.

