### Study aim and objectives

The aim of this study is to determine the effectiveness and acceptability of a complex, multifaceted intervention in reducing the level of PIP in primary care. The intervention combines academic detailing, medicines review with web-based pharmaceutical treatment algorithms that provide recommended alternative treatment options, and tailored patient information leaflets. The intervention development was informed by the Medical Research Council (MRC) guidelines for the development and evaluation of randomized controlled trials (RCTs) [27,28]. It was piloted with a group of five GPs and found to be feasible and acceptable within this group.

Secondary objectives are to evaluate the effect of the intervention on patient outcomes in terms of the number of GP visits, the number of hospitalizations, patient well-being, beliefs about medicines and health status. The views and experiences of participants concerning the possible reasons for the intervention to be effective or ineffective will be explored using qualitative methodology. In addition, an economic evaluation will be carried out.

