## Methods/design

### Trial design

The OPTI-SCRIPT study is a pragmatic two-arm cluster RCT, incorporating qualitative analysis. Qualitative approaches can contribute in several ways to the development and evaluation of health interventions; they have been used during intervention development and piloting and will be used to undertake a process evaluation of the trial [29]. The study design was developed in line with the Consolidated Standards of Reporting Trials (CONSORT) statement extension to cluster RCTs [30]. A cluster design was chosen to avoid the possibility of contamination across arms. A GP who is treating both intervention and control patients might find it difficult to behave differently towards each group [31]. The trial will be conducted in primary care with GP practices as the unit of randomization. A practice can be a single-handed GP or can comprise two or more GPs (group practices); however, not all GPs in group practices may wish to participate. Participation may be decided by one GP on behalf of the group practice, in which case that GP will be the main point of contact for the study. We will keep a record of participating GPs. Participation in the intervention arm will be defined as attendance at the academic detailing visit and undertaking medicines reviews, while participation in the control group as providing patient prescription data. Practices that do not meet these criteria will be considered lost to follow-up (see Figure 1). The intervention will be delivered at the GP level while the unit of analysis will be at the individual patient level, in terms of medicines prescribed, adjusting for clustering.

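### Every intervention-arm interview date depends on a review having been done, so GPs who stop early or never start, and patients never reviewed, have no interview time point

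*Protocol article*

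**What the plan says.** The section Study aim and objectives sets out to "determine the effectiveness and acceptability of a complex, multifaceted intervention". It adds that participants' views on why the intervention did or did not work will be explored qualitatively.

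The Qualitative evaluation section gives the sampling rule: "A random sample of participants in the intervention arm will be invited to participate". On size, "a sample of 10 to 15 patients and 10 GPs is proposed". One of the interview questions is "What barriers, if any, were experienced by GPs in relation to implementing the alternative recommended treatments".

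The same section then fixes the timing:
- Patients: "For individual patients, the interviews will take place within one month of the medicines review".
- GPs: "For GPs, the interviews will be conducted within one month of them completing their assigned reviews", which is spelled out as "after all ten reviews for single-handed practices and after completion of assigned reviews in group practices".

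The Trial design section states: "Participation in the intervention arm will be defined as attendance at the academic detailing visit and undertaking medicines reviews". Intervention practices that do not meet this are classed as lost to follow-up.

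**The concern.** Acceptability is judged partly by whether people take the intervention up and see it through. A GP who found the reviews unworkable and stopped, or a patient who never came for one, has direct knowledge of why delivery failed. The interview schedule has no date for either of them.

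If the trial shows no effect and many reviews were not done, the process evaluation would be expected to explain why. Under the schedule as written, it would hear mainly from those who delivered or received the review. Conclusions on acceptability, sustainability and barriers would lean in that direction, and nothing in the interview data would reveal by how much.

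**Working it through.** The plan gives no figure to reproduce. The check sets the relevant sections of the protocol article side by side, followed by an illustration.

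**1. Who has an interview date under the stated timing**

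| Person | Date available? |
|---|---|
| Single-handed GP who did all ten reviews | Yes |
| Group-practice GP who did all assigned reviews | Yes, even if a colleague stopped |
| GP who did some reviews and stopped | No |
| GP who never started or skipped detailing | No |
| Patient who was reviewed, prescription changed or kept | Yes, even if the practice did not finish |
| Patient never reviewed | No |

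The definition of participation in Trial design points the same way for practices that never start. A practice that did some reviews arguably meets that definition, yet its GP still has no date, because the GP rule requires completion.

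**2. Whether another source fills the gap**

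- Outcome forms (Intervention; Evaluation data) are completed at the end of a review. A GP who stops after four reviews leaves four forms with decisions and reasons. The absent forms show how many reviews were not done, but not why.
- Data management and protection says that, apart from reminders, the team will not monitor how GPs carry out the protocol after the detailing visit.
- The brief telephone interviews without a review trigger are for control-group GPs only.

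No planned source therefore records the reasons for non-delivery.

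**3. Illustration of what the timing rule removes**

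Inputs: 22 practices and 220 patients (Sample size). Assumption: equal allocation, so 22/2 = 11 intervention practices and 220/2 = 110 intervention patients. Non-completion is not given, so 10%, 20% and 30% are assumed values.

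With m unreviewed patients among 110 and s interviews drawn at random without restriction, the chance of including at least one unreviewed patient is 1 − C(110 − m, s)/C(110, s).

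| Assumed non-completion | m | s = 10 | s = 15 |
|---|---|---|---|
| 10% | 11 | 0.67 | 0.82 |
| 20% | 22 | 0.90 | 0.97 |
| 30% | 33 | 0.98 | above 0.99 |

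For GPs, assume one per practice and one non-completing practice. A random 10 of 11 includes that GP with probability 10/11 = 0.91.

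If the dates are followed as written, the expected number of such interviewees is about zero in each case. A truly unrestricted random sample would probably reach some of these people, and the timing rule works against that.

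**The case against.** The strongest reply is that the text sets timing and not eligibility. The frame is stated separately as a random sample of the intervention arm, Evaluation data places interviews simply after the intervention, and no sentence excludes non-completers. This stands in part. A reader might infer that these people can never be sampled, but the document does not say so. It gives them no date and no alternative route, which is a narrower defect.

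A second reply is that failure to change prescribing differs from failure to deliver the review. This stands. A reader might infer that everyone for whom the intervention failed is missed. In fact, reviewed patients whose prescription was maintained have a date, as do GPs who completed their reviews. The questions on barriers, on reactions to changing medication and on the usefulness of the review suit them well. They can also voice unfavourable views. Nor is the sample completers only: a patient needs only their own review. Reminders and a negotiable extension help slow practices to reach the anchor.

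A third reply is that the 10% in Sample size is an allowance for loss to follow-up, not a rate of uncompleted reviews, and that group practices may supply several GPs, so the number of GPs is unknown. This stands, which is why the figures above are illustrative only.

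A last reply is that an article may leave contact with withdrawn participants to the full protocol. That would answer a missing detail. Here the article states a timing rule, and the rule itself causes the tilt.

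**Conclusion.** The point holds in limited form. As written, the interview schedule offers no time point to GPs who stop early or never start, or to patients never reviewed, and no other planned source records why reviews were not done. The findings on acceptability and on reasons for ineffectiveness will therefore lean towards those who delivered or received the review.

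The size is unknown because the document gives no non-completion rate; if all reviews are done, there is no effect. The probabilities shown rest on equal allocation, assumed non-completion of 10% to 30% and, for GPs, one per practice with one non-completing practice.

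The stronger conclusion, that these people are barred from selection and that acceptability is answered by completers alone, is not supported. The primary outcome analysis and the sample size are unaffected. The change is worth making because acceptability is a named aim and the correction is cheap.

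**What to change.** In the Qualitative evaluation section:

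1. State that the interview frame is all GPs and patients allocated to the intervention arm, whether or not reviews were done.
2. Keep the one-month timing for completed reviews.
3. For GPs who did not complete and patients not reviewed, add a time point at the end of the practice's review window, including any agreed extension, or at the practice's withdrawal.
4. Include some of these GPs and patients within the planned 10 GP and 10 to 15 patient interviews, and say whether they are drawn at random or chosen purposively.

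The cost is a change of wording and a short addition to the topic guide, which is still to be developed. The number of interviews need not rise. Trial status reports that patient recruitment was only just beginning, so the change was practicable then. The downsides are that non-completers are less likely to accept an interview and that, if they are chosen purposively, the sample is no longer purely random. Both should be reported with the findings.
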